#### Secondary endpoints

Secondary endpoints include: 1) intradialytic LV chamber quantification and deformation (longitudinal function with speckle tracking) and LV diastolic function; 2) the intradialytic hemodynamic profile of SBP, DBP, MAP and PP; 3) organ and tissue damage, such as the release of specific cellular components; and 4) patient-reported symptoms and thermal perceptions during each modality.

### Statistical methods

Descriptive data will be represented as mean ± standard deviation (SD), median (interquartile range) or number (percentage), when appropriate. The between-treatment number of IDH episodes (based on an intradialytic nadir in SBP as described above) will be analyzed using regression analysis with a Poisson distribution. The mean inter-treatment variability of continuous variables will be calculated using generalized linear mixed effects models with a random intercept, random slope or both, based on the lowest Aikaike’s Information Criterion. A two-sided *p-*value ≤0.05 is considered statistically significant. Statistical evaluations will be performed using IBM SPSS Statistics version 26.0 (Chicago, IL, USA) or RStudio version 1.1.456.

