### Objectives

The primary objective of the HOLLANT study is to evaluate whether intradialytic hemodynamic stability is better preserved during HV-HDF, by comparing the frequency of intradialytic hypotensive episodes between S-HD, C-HD, LV-HDF and HV-HDF. The main secondary objectives include intradialytic signs of tissue damage as measured by Speckle Tracking Echocardiography (STE), a diversity of laboratory parameters, and patient reported outcome measures (PROMs), such as tolerance and cold (sensations).

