#### Hemodynamic monitoring

Diastolic (DBP) and systolic (SBP) blood pressure, pulse pressure (SBP minus DBP), mean arterial pressure (MAP: [(SBP + 2*DBP)/3]), heart rate (HR) and intradialytic hypotensive episodes (IDH, see Primary endpoint) will be recorded before, after and during each dialysis treatment every 30 min (during the first week of every treatment modality) and every 15 min (during the second week). Measurements will be performed with a manometric cuff in different sizes, which is connected to the dialysis machine (automatic blood pressure measurement cuff, B. Braun Avitum AG, Melsungen, Germany).

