### Endpoints

#### Primary endpoint

The primary endpoint of this study is an absolute intradialytic nadir in SBP of < 90 and < 100 mmHg for patients with a predialysis SBP < 159 and ≥ 160, respectively.

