If HV-HDF appears indeed to be associated with a better intradialytic hemodynamic profile and less tissue damage, this will enhance our understanding why HDF is associated with a superior patient outcome and allow the nephrological community to improve this treatment modality even further. If not, the outcome of this study will anyhow teach us if, and to what extent intradialytic hemodynamic instability is associated with tissue injury and patient discomfort, and thus help the medical staff to optimize dialysis treatment in individual cases.

The largest strength of this study is its randomized cross-over design, which prevents that inter-individual differences, such as co-morbidity and prescribed medication, influence the results. An important limitation may be the duration of each dialysis modality, which may be too short to answer all questions. Yet, to minimize patients’ discomfort the underlying protocol was designed in its current form. Since this study is primarily designed to investigate the intradialytic hemodynamics and its consequences on organ and tissue damage between the four most practiced extracorporeal dialysis techniques (S-HD, C-HD, LV-HDF and HV-HDF), potential differences in thermal and sodium balance are not addressed. Another important issue of any study with a cross-over design is the duration of the wash-out period that will most likely prevent carry-over effects of the previous modality. For this study, a wash-out period of 1 week (the first week of every treatment modality) was arbitrarily chosen, since relevant information on this topic is absent.

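### The primary endpoint is a yes/no nadir per session, but the analysis is a Poisson regression on a number of episodes; the counting unit is unsettled and the Poisson variance fits neither reading

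*Protocol article*

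**What the plan says.** Primary endpoint: "The primary endpoint of this study is an absolute intradialytic nadir in SBP of < 90 and < 100 mmHg", the limit depending on predialysis pressure. A nadir is the lowest value of a session, so the endpoint is met or not met once per session. Sample size considerations follows that reading: it powers a 40% lower risk (relative risk 0.60) of the endpoint occurring.

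Three other places speak of episodes. Objectives evaluates stability "by comparing the frequency of intradialytic hypotensive episodes between S-HD, C-HD, LV-HDF and HV-HDF". Hemodynamic monitoring says that "intradialytic hypotensive episodes (IDH, see Primary endpoint) will be recorded before, after and during each dialysis treatment every 30 min" in the first week of each modality, and every 15 min in the second. Statistical methods says that the "number of IDH episodes (based on an intradialytic nadir in SBP as described above) will be analyzed using regression analysis with a Poisson distribution".

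The next sentence of Statistical methods assigns "generalized linear mixed effects models with a random intercept, random slope or both", but for continuous variables only. For the primary outcome the article names a distribution and nothing on how sessions from the same patient are handled.

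**The concern.** Two things are left loose in the sole primary analysis. First, the unit: one yes/no result per session, or every dip below the limit. Second, the variance: a Poisson model sets it equal to the mean. Repeated yes/no sessions within a patient vary less than that. Clusters of dips within one session vary more. The standard error is therefore off under either reading, in opposite directions. At stake is either power, in a trial expecting about 32 completers, or the 5% error rate of the primary test.

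**Working it through.** **Inputs from the article.** 40 patients and about 20% loss give 40 × 0.80 = 32 completers. Two-week periods at three sessions a week give 6 sessions per modality, or 3 if the first week, called a wash-out in the Discussion, is left out of the analysis. Relative risk 0.60, two-sided 0.05.

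**Assumed, because the article does not give them.** Session risk 10-30%, patient SD 1.2 or 1.5 on the logit scale, and the number of episodes in an affected session.

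**The plan's own figure.** The step from 32 to 40 reproduces (32/0.80 = 40). The 80% power (printed as β = 0.80) cannot be checked, because no baseline risk or within-patient correlation is stated. For scale, with independent sessions and Poisson variance the reference modality needs (1.960 + 0.842)² × (1 + 1/0.60) / (ln 0.60)² ≈ 80 events. That is a session risk of 80/192 = 42% with 6 sessions or 80/96 = 84% with 3. With a yes/no variance the risks needed are 32% and 51%.

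**Step 1: one result per session, identical patients.** Let T0 and T1 be the event totals on two modalities. The plain Poisson SE of ln(T1/T0) is √(1/T0 + 1/T1). At 20% risk and 6 sessions the expected total is 32 × 6 × 0.20 = 38.4 per modality.
- Poisson SE: √(2/38.4) = 0.228.
- Yes/no SE: √(2 × 0.80/38.4) = 0.204.
- Actual type I error: P(|Z| > 1.96/√0.80 = 2.19) = 2.8%.

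**Step 2: patients differ in risk.** The within-patient variance factor becomes 1 − E(p²)/E(p), which is smaller still, so the gap widens. The clustered SE used for comparison is √[n/(n−1) × Σ(y1/T1 − y0/T0)²], summed over patients. Simulations with 32 patients and one pairwise contrast gave:

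| Setting | Poisson variance | Patient-clustered |
|---|---|---|
| Type I, SD 1.2, risk 10-30%, 3 or 6 sessions | 1.0-2.6% | 4.4-5.2% |
| Type I, SD 1.5, same grid | 0.5-2.1% | 4.9-5.7% |
| Power, SD 1.2, risk 30%, 6 sessions | 72% | 83% |
| Power, SD 1.2, risk 30%, 3 sessions | 36% | 52% |
| Power, SD 1.5, risk 20%, 6 sessions | 50% | 65% |

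Across the SD 1.2 grid the power lost is about 4-16 points. At SD 1.5 it runs from about 8 (17.9 − 10.3) to 22 (56.7 − 35.0).

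**Step 3: several episodes per session.** Suppose an affected session carries 1 + Poisson(λ) episodes. The variance-to-mean ratio is [λ + (1+λ)²]/(1+λ) − p(1+λ). With λ = 1 and p = 0.20 this is 2.5 − 0.4 = 2.1, so type I error is P(|Z| > 1.96/√2.1 = 1.35) ≈ 18% for identical patients. Simulation at SD 1.2 gave 13-26% against 5-6% clustered. At SD 1.5, with a mean of 1.5-3 episodes per affected session, it gave 7.7-24.4% against 5.8-7.6%.

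**Step 4: treatment response differs between patients.** With one result per session and a response SD of 1.0-1.5, plain Poisson rejected in 1.8-11.1% of runs. It exceeded 5% only in six-session settings.

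**Step 5: would a patient intercept cure it?** In one complete balanced data set, pooled Poisson gave −0.070 with SE 0.187. Poisson with patient fixed effects gave the same estimate and the same SE. The patient-clustered robust SE was 0.145. The cause is the variance assumption, not the absence of a patient intercept.

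**The case against.** The strongest reply is that this is a condensed article. "will be analyzed using regression analysis with a Poisson distribution" names a distribution; it does not exclude a patient effect or a robust variance, and the full protocol or SAP may specify either. A modified Poisson GEE would even be consistent with that sentence. This stands: a reader might infer that the primary model is a plain Poisson regression that ignores patients, but that would be inference from silence.

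A reader might also infer inflated false positives. The article does not support that as the main reading. It ties episodes to the nadir and powers a risk, which favours one result per session, and there the test is mainly conservative.

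Nor does the model contradict the Discussion, which says that the cross-over "prevents that inter-individual differences, such as co-morbidity and prescribed medication, influence the results". In complete data every patient contributes to all four modalities, so the contrast is already balanced over patients. An over-wide SE wastes precision but does not bias the comparison.

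What the reply does not remove is printed: a nadir endpoint powered as a risk, an analysis of a number of episodes, a named Poisson distribution, and random effects assigned only to continuous variables.

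**Conclusion.** The concern holds in this limited form. The counting unit of the primary outcome is not settled, and the stated Poisson analysis, followed literally, gives miscalibrated standard errors. On the more natural one-per-session reading the intervals are mainly too wide: type I error about 1-2.6%, and about 4-16 points of power lost at a relative risk of 0.60. If several episodes per session are counted they become too narrow (type I error about 13-26%), and they can also do so if treatment response varies strongly between patients. The direction on each reading follows from the variance formulas. The sizes rest on assumed session risks, patient SDs and episode counts, none of which is in the article. It is not shown that the trial's full analysis plan omits within-patient clustering.

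**What to change.** Under Primary endpoint and Statistical methods, state that the primary outcome is session-level intradialytic hypotension, yes or no, at most one per session. Analyse the sessions with one of two models, named in advance:
- a log-link (modified Poisson) GEE clustered on patient, with robust, small-sample-corrected variance; or
- a binomial/logistic mixed model with a patient random effect.

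In either, enter modality and period as fixed effects. If sessions are aggregated to counts for the GEE, add an offset of the log number of sessions. If the full protocol or SAP already specifies such a model, align the published wording with it.

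The cost is a wording change. No extra data are needed, and the software already named can fit these models. The article reports 25 of 40 patients included, so the change can be made while recruitment is still under way.

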#### Non-invasive advanced hemodynamic monitoring

During the first or second dialysis of the last week of every treatment modality, every 20 seconds MAP, stroke volume (SV), heart rate, total peripheral resistance and cardiac output (CO) will be obtained using the Clearsight monitor (BMEYE/Edwards Lifesciences, Amsterdam, The Netherlands), which is a non-invasive arterial pressure measuring device. This monitor turns finger arterial pressure with a fast-pneumatic system to account, as well as photoplethysmography to detect changes in finger arterial diameter during inflations [56]. A volume clamp method is used whereby rapid variations in the cuff pressure allow maintenance of a constant arterial diameter, with an automatic algorithm (Physiocal). The pressure within the cuff is therefore reflective of finger arterial pressure [56]. The Clearsight finger cuff will be attached to the mid-phalanx of the third digit of the hand at the contralateral side of the dialysis shunt. The heart reference system will be placed on the middle of the left side of the thorax. The measured hand and the manometric arm cuff are placed at the mid-thorax to account for hydrostatic pressure differences.

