#### 2D speckle tracking echocardiography

Speckle Tracking Echocardiography (STE) will be performed before, after 1 and after 3 h of treatment during the last dialysis of each modality. Two-dimensional left ventricular (LV) measurements of wall thickness and cavity diameters, 2D biplane Simpson measurement of volumes and ejection fraction are measured using a commercial scanner (Affiniti 70C, Philips Healthcare, The Netherlands) with a fully sampled matrix array (S5–1) transducer. These measurements are indexed for body surface area (BSA). For the assessment of global longitudinal deformation (GLS) as well as distribution of regional longitudinal strain, 2DSTE is performed from an apical position. Diastolic LV function is measured by 2D LAVI (left atrial volume index), transmitral E/A ratio and deceleration time, e’ wave velocity, E/e’ ratio and SPAP (systolic pulmonary artery pressure). Estimated right ventricular function will be done by TAPSE (tricuspid annular plane systolic excursion), s’ wave velocity and RV (right ventricular) regional and global strain. The data will be recorded electronically and assessed off-line by a trained research physician in Xcelera Cardiology Information Management Version 4.1 (Philips Healthcare, The Netherlands).

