#### Sample size considerations

We plan to include 40 patients. Loss to follow-up (due to an event) is expected to be about 20%. The number of patients with complete follow-up will be sufficient to detect a 40% lower risk (relative risk of 0.60, α = 0.05, β = 0.80) in the occurrence of the primary endpoint. The power calculation applied was designed for cross-over studies [60].

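### Letting AIC choose between random intercept and slope, with no session or patient-by-modality term named, can leave modality tests on repeated intradialytic readings anti-conservative

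*Protocol article*

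**What the plan says.** Under Statistical methods, the protocol article says continuous variables will be analysed with "generalized linear mixed effects models with a random intercept, random slope or both, based on the lowest" value of Akaike's criterion. A two-sided p-"value ≤0.05 is considered statistically significant". The text does not say over which unit the intercept or slope varies (patient, period or session), or whether the slope is on time or on modality. It names no session or patient-by-modality term.

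The data these models must handle are described elsewhere in the Methods:

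- Study design and Table 1: four modalities of two weeks each, three sessions a week, each session fixed at 4 h.
- Hemodynamic monitoring: cuff pressures "every 15 min (during the second week" of each modality).
- Non-invasive advanced hemodynamic monitoring: "every 20 seconds MAP, stroke volume (SV), heart rate" and other Clearsight variables, in one session per modality.
- 2D speckle tracking echocardiography (STE): "before, after 1 and after 3 h of treatment during the last dialysis of each modality".
- Patient tolerance and Blood sampling: thermal perception (VAS-TP) at three times, blood at two times in one session, and the symptom index (DSI) once per period.

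**The concern.** The data have four levels: reading, session, modality period and patient. Readings in one session share that day's fluid state, cuff placement and timing. They are not independent replicates of the modality effect, because modality changes only between periods. A model with a patient intercept, or a patient intercept and a time slope, leaves this shared variation in the residual and treats each reading as separate evidence. The standard error of a modality difference is then too small. AIC can only rank the models it is offered, so it cannot restore a variance component that no candidate carries.

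The stake is the mechanistic part of the trial. The Discussion makes the hemodynamic profile the second aim and plans to relate it to tissue injury and tolerance. A false modality difference in blood pressure would feed directly into that explanation.

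**Working it through.** **Inputs from the article.** Planned enrolment: "We plan to include 40 patients". "Loss to follow-up (due to an event) is expected to be about 20"%, which leaves 40 × 0.80 = 32 completers. Cuff readings per second-week session: 240/15 + 1 = 17. Clearsight readings per session: 4 × 3600/20 = 720. STE: 3. VAS-TP: 3, taken here in one session. Blood: 2. DSI: 1. I assume the three second-week sessions are analysed, since the Discussion calls the first week of each modality a wash-out.

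**The plan's own figure.** There is none for the continuous models. The only calculation is for the primary endpoint ("relative risk of 0.60, α = 0.05, β = 0.80"). Its 32/(1 − 0.20) = 40 is consistent. Its power cannot be checked without a baseline risk, and it does not bear on this point.

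**Assumption.** The article gives no variance components. Let ρ be the within-session intraclass correlation (ICC) after removing the patient effect. It is shown as a range.

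**Analytic check, patient intercept only.** The variance of a modality contrast is understated by a factor DE = 1 + (m − 1)ρ, where m is the number of readings per session. The actual error of a nominal 5% test is 2 × [1 − Φ(1.96/√DE)].

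- Cuff, ρ = 0.20: DE = 1 + 16 × 0.20 = 4.2; 1.96/√4.2 = 0.956; error 34%.
- Cuff, ρ = 0.50: DE = 1 + 16 × 0.50 = 9.0; error 51%.
- STE or VAS-TP, ρ = 0.05 to 0.50: DE = 1.1 to 2.0; error 6% to 17%.
- Blood, same range: DE = 1.05 to 1.5; error 6% to 11%.
- DSI: m = 1, DE = 1; error 5%.
- Clearsight, if all 720 raw values are modelled, ρ = 0.05: DE = 1 + 719 × 0.05 ≈ 37; error about 75%.

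**Simulation for cuff pressure.** No true modality effect; 32 patients × 4 modalities × 3 sessions × 17 readings; 3,000 runs per setting. Assumed SDs in mmHg: patient 20, patient time slope 8, residual 10, session 0, 3, 5 or 10. ICC = s²/(s² + 100) = 0, 0.08, 0.20, 0.50. Wald test of one modality contrast at 1.96. Type I error (%):

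| Model | ICC 0 | 0.08 | 0.20 | 0.50 |
|---|---|---|---|---|
| Patient intercept | 4.2 | 18.5 | 34.0 | 52.7 |
| Intercept + time slope | 4.8 | 19.9 | 35.1 | 53.2 |
| AIC between these two | 4.8 | 19.9 | 35.1 | 53.2 |
| Intercept + modality slope | 4.1 | 5.3 | 5.6 | 5.7 |
| AIC: intercept or modality slope | 4.2 | 5.3 | 5.6 | 5.7 |
| AIC: intercept, time slope or modality slope, slopes not combined | 4.8 | 19.8 | 27.5 | 5.7 |
| Intercept + session effect | 4.2 | 5.0 | 4.8 | 5.1 |

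The sixth row shows why the rule is unsafe. At ICC 0.08 AIC chose the time slope in 99.9% of runs, and at 0.20 in about 76%. The time slope fitted better, but it does nothing to protect the modality test. The simulation included no separate patient-by-modality variance. Where such variance exists, a session effect alone would not carry it.

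**The case against.** The strongest reply is that the article does not commit to the failing model. It does not say that the intercept or slope is at patient level, or that the slope is on time. Each modality occupies exactly one period, so a patient-level random slope on modality is itself a patient-by-period effect. It fits the stated wording and holds error at 5-6%. When only that slope competes with the plain intercept, AIC picks it in at least 99% of runs once the ICC is 0.08 or more. All of this stands. A reader might infer that the plan necessarily treats readings as independent; the text does not support that.

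Second, an intradialytic profile may be tested as modality by time, and a shift shared by a whole session cancels from that contrast. In a simulation with a patient intercept only, the interaction test rejected in 0.9-4.4% of runs when sessions differed by level alone, and in about 2-19% when session slopes with SD 5-10 mmHg were added. For three STE-like readings it rejected in about 1-8%. So the inflation belongs mainly to the modality main effect.

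Third, a reader might infer that standard errors are several times too small for every continuous outcome. For STE at ICC 0.50 the factor is √2 = 1.4; for cuff pressure at 0.20 it is √4.2 ≈ 2.0; DSI is unaffected. The large Clearsight figure requires that raw 20-second values enter the model, and the article describes only how they are acquired.

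Finally, grouping levels and covariance structure are often left to a full protocol or analysis plan, which is not shown. That would dispose of a bare omission. Here the article fixes a candidate set and a data-driven selection rule, and that rule can select an invalid structure.

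**Conclusion.** The point holds conditionally and is of moderate severity. The stated rule permits both a test near its nominal level and one with several times the nominal error, and leaves the choice to fit. If it is applied as a patient intercept with or without a time slope, cuff-pressure modality main effects carry about 19-53% type I error over ICCs of 0.08-0.50. The other repeated outcomes are affected roughly in line with their number of readings per session.

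These sizes rest on assumed variance components; with no session variance there is no inflation. The point covers secondary continuous outcomes. A reader might extend it to the primary endpoint, but the number of hypotensive episodes is analysed by Poisson regression, which this finding does not address.

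**What to change.** State the grouping levels and the slope variable. For cuff pressure, Clearsight, STE and VAS-TP, pre-specify:

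- a patient random intercept;
- a patient-by-modality random effect (equivalent here to patient-by-period);
- a session-within-period random effect where several sessions per period are analysed;
- a session-level time slope if time trends are tested.

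Alternatively, reduce the readings to one summary per session or period and model that; several session summaries per period still need the patient-by-modality effect. Either way, AIC should not decide whether this variance is modelled.

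The cost is a few lines of text and one or two random terms in the mixed models already planned. Confidence intervals for the secondary outcomes will be wider where session or period variance exists. Sample size and data collection do not change.

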#### Sample size considerations

We plan to include 40 patients. Loss to follow-up (due to an event) is expected to be about 20%. The number of patients with complete follow-up will be sufficient to detect a 40% lower risk (relative risk of 0.60, α = 0.05, β = 0.80) in the occurrence of the primary endpoint. The power calculation applied was designed for cross-over studies [60].

